**Figure 2 F2:**
[figure not shown]
Location of acupoints and non-acupoints.

The specific operations will be as follows: the rubber ring on the PSD base will be removed first to introduce a disposable filiform needle with the needle tip exposed. Then, the needles will be advanced at the selected acupoints, and the direction and depth of acupuncture will be strictly under the basic requirements of acupuncture operation. Following needle insertion, the needles will be modestly lifted and twirled to get local distension until *de qi* (a component sensation, including soreness, numbness, distension, and heaviness). Within 30 min, manual manipulation for each acupoint lasted 10 s and will be repeated three times with intervals of 10 min.

#### Sham Acupuncture Group

The sham acupoints of ST25, SP14, and ST37 will be selected to perform sham acupuncture without skin penetration (Table 2 and Figure 2). We will formulate and follow the standardized step-by-step instructions and operations to use the same rituals in the VA and SA groups as far as possible. However, instead of penetrating the skin, the blunt needles will be retracted into the hollow needle handle without penetrating the skin or reaching *de qi*. The frequency and course of treatment will be the same as those in the VA group.

### Outcome Measures

Among many persistent symptoms of SCC, reduced bowel movements are the major symptom for clinical diagnosis. An epidemiological survey showed that the most troublesome symptoms for 75% of patients are the fewer weekly bowel movements and the delayed defecation at the anus/rectum (3, 11). Therefore, bowel movements, spontaneous defecation or not, complete evacuation or not, degree of straining, stool consistency (according to Bristol stool form scale [BSFS]), and patients' QOL will be used as indicators to present the efficacy of acupuncture.

#### Primary Outcome Measurement

The primary outcome will be the proportion of patients with 3 or more mean weekly complete SBMs (CSBMs) over weeks 1–4 and 5–8. The mean weekly CSBMs will be calculated by dividing the sum of the CSBMs during weeks 1–4 or 5–8 by 4. The proportion of patients with mean weekly CSBMs ≥ 3 will be divided by the number of observed participants in this group, and then multiplied by 100% (11). One SBM refers to the bowel movement that occurs in the absence of rescue medicine, or other auxiliary techniques (laxatives, suppositories usage, or manual assistance) within the preceding 24 h; while one CSBM refers to an SBM with the sensation of complete evacuation.

#### Secondary Outcome Measurement

1. The proportion of patients with ≥ 1 increase of mean weekly CSBMs from baseline over weeks 1–4, 5–8.

The proportion of patients with mean weekly times of CSBMs ≥ 1 will be divided by the number of observed cases in this group, and then multiplied by 100%. Assessing time frame: weeks 1–4, 5–8.

2. The change from baseline in the mean score of straining of each SBM over weeks 1–4, 5–8.

The straining degree of each SBM will be evaluated using the following scale (10–12): no difficulty is 0; a little difficult, need some straining to defecate is 1 point; difficult, need straining to defecate is 2 points; very difficult, need hard straining or even auxiliary defecation is 3 points. The mean score of straining of each SBM will be calculated by dividing the total score of straining all SBMs by the sum of SBMs times in weeks 1–4 and 5–8, which will then be subtracted by the score of straining in the first visit.

3. The change from baseline in the mean score of stool consistency of each SBM over weeks 1–4, 5–8.

Participants will self-report their stool consistency of each SBM according to the 7-type BSFS (32): type 1 is separated hard lumps; type 2 is sausage-shaped but lumpy; type 3 like a sausage but with cracks on its surface; type 4 like a sausage or snake, smooth and soft; type 5 is soft blobs with clear cut edges (passed easily); type 6 is fluffy pieces with ragged edges, a mushy stool; type 7 is watery, no solid pieces, entirely liquid. The total score of stool consistency for SBMs will be divided by the summed times of SBMs during weeks 1–4 and 5–8 as the mean stool consistency for each SBMs; then will be subtracted by the score of BSFS in the first visit.

4. The change from baseline of the score of self-rated Patient Assessment of Constipation Quality of Life (PAC-QOL) at week 4.

PAC-QOL is a self-report questionnaire to evaluate the quality of life in participants with constipation, which was distributed by Mapi Research Trust in France. This questionnaire contains 28 items including 4 basic parts of physical discomfort (items 1–4), psychosocial discomfort (items 5–12), worries and concerns (items 13–23), and satisfaction (items 24–28).

The questionnaire will be scored with 5 grades, and all kinds of discomfort will be assigned 0–4 points according to the degree of discomfort from “none” to “maximum,” in which the items 18, and 25–28 are reversed. The score of each dimension is the average score of all items in this dimension, and the total score is the average score of all items.

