**Secondary outcomes**
Proportion of patients with ≥ 1 increase of mean weekly CSBMs from baseline over weeks 1–4 and 5–8		**×**	**×**	**×**				**×**
Mean score of straining of each SBM		**×**	**×**	**×**				**×**
Mean score of stool consistency of each SBM		**×**	**×**	**×**				**×**
PAC-QOL		**×**	**×**	**×**				**×**

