#### Inclusion Criteria

Participants meeting all the following conditions will be enrolled in this study:

Aged 18 to 60 years old;History of SCC for a minimum of 6 months before the screening visit, and the activity of symptoms last for at least 3 months;Two or fewer CSBMs per week, exertion in defecation, and lumpy or hard stools (Bristol Stool Form Scale [BSFS] ≤3) during the run-in period;No special eating habits and not accompanied by severe anxiety, depression, or other mental disorders (SAS or SDS score <75);No use of medicine for constipation during the 1 week before enrolment (except for rescue medicine), including intestinal microecological preparations, probiotics, etc.; no acupuncture treatment for constipation in the previous 1 month; no participation in any other ongoing trial;Volunteered to join this trial and signed the informed consent.

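### Secondary outcome 1 is named as a rise of at least 1 weekly CSBM from baseline, but its formula has no baseline term and so counts some patients who entered at 1–2 CSBMs and did not improve as responders

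*Protocol article*

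**What the plan says.** In the protocol article, item 1 of Secondary Outcome Measurement is headed "The proportion of patients with ≥ 1 increase of mean weekly CSBMs from baseline over weeks 1–4, 5–8". Table 1 lists the same outcome in the same sense: "Proportion of patients with ≥ 1 increase of mean weekly CSBMs from baseline over weeks 1–4 and 5–8". Both describe a change from baseline.

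The calculation sentence directly under the heading takes as its numerator "The proportion of patients with mean weekly times of CSBMs" at or above 1. At greater length it reads "The proportion of patients with mean weekly times of CSBMs ≥ 1 will be divided by the number of observed cases in this group", followed by multiplication by 100%. It contains no baseline value and no subtraction.

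Three other places bear on how that sentence must be read:

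- Primary Outcome Measurement defines the quantity: "The mean weekly CSBMs will be calculated by dividing the sum of the CSBMs during weeks 1–4 or 5–8 by 4". That is a level over a four-week window, not a change.
- Items 2 and 3 of Secondary Outcome Measurement (straining and stool consistency) state expressly that the first-visit score is subtracted. Item 1 does not.
- Inclusion Criteria admit patients with "Two or fewer CSBMs per week, exertion in defecation, and lumpy or hard stools" during the run-in, so a patient may enter with 0, 1 or 2 CSBMs in that week.

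Nothing else in the article corrects or overrides the item 1 formula.

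**The concern.** One endpoint has two definitions, and they select different patients. The name asks whether a patient has gained at least one CSBM per week. The formula asks whether the patient has at least one CSBM per week. The eligibility ceiling is 2, so some patients can meet the formula's threshold before any treatment is given.

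An analyst who programs the sentence as written would report a figure that does not match its label. The responder rate would be too high wherever patients with a baseline of 1 or 2 are present, and patients with no gain, or a loss, would be counted as successes. An analyst who follows the name would report something else. Two usable definitions also leave room to choose between them after the data are seen.

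**Working it through.** The article gives no rate, power or sample-size figure for this outcome, so there is nothing to reproduce. The check compares the two rules case by case and then illustrates the size under stated assumptions.

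**Inputs from the article.** Let b be the run-in weekly CSBM count, 0, 1 or 2 (Inclusion Criteria; one-week run-in in Trial Design). Let m be the mean weekly CSBMs in a window, the four-week sum divided by 4 (Primary Outcome Measurement).

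- Named rule: responder if m − b ≥ 1.
- Written formula: responder if m ≥ 1.

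**Case comparison.**

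| b | m | Course | Written formula | Named rule |
|---|---|---|---|---|
| 0 | 0 | unchanged | no | no |
| 0 | 1 | gain of 1 | yes | yes |
| 1 | 1 | unchanged | yes | no |
| 1 | 1.5 | gain of 0.5 | yes | no |
| 1 | 2 | gain of 1 | yes | yes |
| 2 | 1 | loss of 1 | yes | no |
| 2 | 2 | unchanged | yes | no |
| 2 | 2.5 | gain of 0.5 | yes | no |
| 2 | 3 | gain of 1 | yes | yes |

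The rules disagree exactly when 1 ≤ m < b + 1. At b = 0 that interval is empty, so they agree. At b = 1 it covers m from 1 to below 2, and at b = 2 it covers m from 1 to below 3.

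**Direction.** Since b ≥ 0, m − b ≥ 1 implies m ≥ 1. Every responder by the named rule is also a responder by the formula, so the formula can overcount but never undercount.

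**Illustration 1: effect on a treatment contrast.** Assumptions not in the article: true named-rule responder rates of 50% and 25%; a share s in each arm that enters at 1–2 and stays at or above 1; and, among the rest, the same response rates p. The rate under the written formula is s + (1 − s)p, so the difference is (1 − s) × 25 points. Power uses the two-proportion normal approximation with pooled null variance, 40 per arm, two-sided 0.05.

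| s | Rates under formula | Difference (points) | Approximate power |
|---|---|---|---|
| 0% | 50% vs 25% | 25 | 64% |
| 10% | 55% vs 32.5% | 22.5 | 53% |
| 30% | 65% vs 47.5% | 17.5 | 35% |
| 50% | 75% vs 62.5% | 12.5 | 22% |
| 67% | 83.5% vs 75.3% | 8.3 | 15% |

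**Illustration 2: no true change.** Assumption not in the article: CSBMs follow a Poisson distribution with an unchanged weekly rate, and the run-in count is conditioned on being 2 or fewer.

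| True weekly rate | Responders, written formula | Responders, named rule |
|---|---|---|
| 0.25 | 1.9% | 1.5% |
| 0.5 | 14% | 9% |
| 1 | 57% | 25% |
| 1.5 | 85% | 35% |
| 2 | 96% | 46% |

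The named rule is not zero here because one-week and four-week counts vary by chance. The gap between the columns is the overcount. It is negligible at very low rates and large near the eligibility ceiling.

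**The case against.** The strongest reply is that the intention is plain. The heading and Table 1 agree, and the faulty sentence closely follows the primary-outcome sentence with the threshold changed from 3 to 1, so the reference to an increase was probably lost in drafting. A careful statistician might well follow the name, and the analysis plan that the article says will be settled before the study starts may already state the numerator. This stands as a reason for moderate severity. It does not make the sentence right: it is the only calculation rule the article gives for this outcome, and it computes something else.

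A reader might infer more than the text supports in four ways:

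- That every unchanged patient becomes a responder. This is true only for a baseline of 1 or 2. Unchanged patients who enter at 0 are scored correctly.
- That the trial loses a known amount of power. The article gives neither a baseline distribution nor expected rates, and its sample size was not derived from this outcome. In a severe population many patients may enter at 0, and a small share s costs little.
- That the error favours acupuncture. The formula applies equally to both arms and, under the illustrated assumptions, shrinks the difference. That dilution is not guaranteed, because the misclassified share could differ between arms.
- That the main efficacy result is compromised. The primary outcome is a level of 3 or more by both its name and its formula.

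**Conclusion.** The contradiction is real and lies within item 1 itself: the named outcome is a change from baseline and the calculation rule is an absolute level. Given the eligibility ceiling of 2, following the rule counts as responders unchanged patients with a baseline of 1–2, patients falling from 2 to 1, and patients gaining less than 1 from such a baseline. Patients entering at 0 are unaffected.

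That the formula can only overcount follows from the definitions and needs no assumption. The dilution of the treatment difference does rest on assumptions: that such patients are common in both arms, in similar shares. Over the assumed range of s from 10% to 67%, a 25-point contrast falls to between 22.5 and about 8 points. These figures, and the power values with them, are illustrations and not estimates for this trial.

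The point should be fixed before analysis. It ranks below a critical defect because the outcome is secondary, its intent can be recovered from its name, and the primary outcome and sample size are untouched.

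**What to change.** Replace the numerator in the item 1 calculation sentence with: the number of participants whose mean weekly CSBMs in the window minus their baseline (run-in) weekly CSBMs is 1 or more. Compute it once for weeks 1–4 and once for weeks 5–8. State that the run-in week supplies the baseline for this item, because items 2 and 3 refer to the first visit and item 1 is silent.

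The correction concerns the numerator only. The choice of denominator is a separate matter and need not change to resolve this contradiction.

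The cost is one sentence, carried through to the analysis plan if it repeats the formula. No new data are needed, since the run-in CSBM count is already required to establish eligibility. The change should be made and dated before unblinded data are seen.

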## Introduction

Chronic constipation refers to a functional bowel disorder except for irritable bowel syndrome (IBS), in which symptoms of difficult, infrequent, or incomplete defecation predominate (1). It affects ~14% of the population worldwide, with a prevalence of 4–6% in China (2, 3). Health-related quality of life (QOL) is negatively affected by the presence of chronic constipation and by its severity (4, 5). Severe chronic constipation (SCC) has distinct duration and severity of symptoms over mild and transient types, generally associated with weekly spontaneous bowel movements (SBMs) of <2 times (6). Even though empirical laxatives are the mainstay for constipated patients, a high level of dissatisfaction has been reported since they often target only 1 aspect of the disease (7). In addition, relief of symptoms is limited to the period of treatment, and efficacy tends to fade after the drug is discontinued (8). One European survey of chronic constipation revealed that almost half were using alternative treatments (acupuncture, cupping, and homeopathy), and nearly 90% of respondents expressed interest in new therapies (9).

Acupuncture is the representative of non-pharmaceutical choice with eminent advantages in the management of SCC. Our previous study revealed that the effectiveness of acupuncture was non-inferior to mosapride in increasing the weekly SBMs, but with a better safety profile (10). The effects of acupuncture could accumulate with 4-week treatments and persist throughout the 4-week follow-up. In addition to the improvement of intestinal discomforts, acupuncture can also bring better QOL to SCC patients with improved mental symptoms such as anxiety and depression (4, 11–13). Gastrointestinal (GI) motor function abnormalities are considered to be of primary importance for SCC symptoms generation. Previous basic researches demonstrated that acupuncture stimulation could improve GI motility, promote contractility of colonic tissue, and facilitate gut transit in constipated animals (14–16). However, the detailed mechanisms underlying acupuncture for SCC remain largely unknown.

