### Trial Design

This trial is designed as a randomized, sham-controlled trial with blinded participants, outcome assessor, and statistician. In this study, 80 eligible participants will be randomized to the verum acupuncture (VA) or sham acupuncture (SA) group with a ratio of 1:1. The total research period will be preceded by a 1-week run-in phase after the screening visit, then following the 4-week treatment phase, and 4-week follow-up phase. Forty healthy volunteers will also be enrolled to serve as a healthy control group. Healthy volunteers will not receive any treatment, and the correlation between gut microbiota and fecal miRNAs will be determined by comparing the constipated patients before treatment with them. The time frame of this trial is presented in Table 1.

**Table 1 T1:** Time points of treatment assessment.

	**Enrollment**	**Baseline**	**Treatment phase**		**Follow-up phase**			
**Time point**	**Week −1**	**Week 0**	**Week 2**	**Week 4**	**Week 5**	**Week 6**	**Week7**	**Week 8**

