### Statistical Analysis

#### Clinical Data Analysis

The statistical analysis plan will be determined before the initiation of the study. Demographic characteristics, baseline characteristics, and efficacy indicators will be analyzed using SPSS 25.0 software according to Full Analysis Set (FAS) and Per Protocol Set (PPS). The missing values in the FAS will be treated using the Last Observation Carried Forward method with the data closest to the first observation. The research results will be mainly based on the results of the FAS, and the results of PPS will be used as auxiliary references.

Continuous variables of normal distribution will be represented by 95% confidence interval, mean and standard deviation. Continuous variables of non-normal distribution will be described by median and inter-quartile range. Classification variables will be described in terms of percentage and frequency. The qualitative data will be compared using the chi-square test. If the quantitative data are normally distributed, we will use the analysis of variance to detect the difference between groups; otherwise, the Mann-Whitney test will be used. The data table will be recorded anonymously and statistical analysis will be carried out by independent statisticians who are blinded to the allocation.

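### The straining and stool-form outcomes have no value for a patient without an SBM, and the stated carry-forward rule cannot supply a run-in baseline and hides an empty 4-week window

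*Protocol article*

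**What the plan says.** Under Secondary Outcome Measurement, item 2 computes the straining score by "dividing the total score of straining all SBMs by the sum of SBMs times" in each 4-week window, "which will then be subtracted by the score of straining in the first visit". Item 3 is built the same way: "The total score of stool consistency for SBMs will be divided by the summed times of SBMs during weeks 1–4 and 5–8", less the stool-form score at the first visit. Neither item says what happens when the number of SBMs is zero.

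Table 1 lists "Mean score of straining of each SBM" among the secondary outcomes and marks it at baseline (Week 0) as well as later. Trial Design says that the study period is "preceded by a 1-week run-in phase", placed after the screening visit. That run-in is the only observation period before Week 0.

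Primary Outcome Measurement does not count a movement as an SBM if rescue medicine or another aid was used in the 24 hours before it. Inclusion Criteria cap complete SBMs at two per week and require straining and hard stools during the run-in. They set no minimum number of SBMs, and they exempt rescue medicine from the pre-enrolment ban on constipation drugs. The Introduction describes the disease as "generally associated with weekly spontaneous bowel movements (SBMs) of <2 times".

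The only missing-data rule, under Clinical Data Analysis, is: "The missing values in the FAS will be treated using the Last Observation Carried Forward method". Results rest mainly on the Full Analysis Set.

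**The concern.** An average per SBM exists only if there is at least one SBM. In this population the count can be zero for a reason tied to severity: a patient who moves the bowel only with help has stools but no SBMs. The straining scale points the same way. Its top grade includes assisted defecation, yet a manually assisted movement is not an SBM, so some of the worst movements never enter the average.

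Two things are at stake, and they differ. A missing baseline arises before treatment. It costs precision and shifts two of the four secondary outcomes towards patients who had a spontaneous movement in the run-in. An empty treatment or follow-up window arises after randomization and can depend on treatment. LOCF fills it with a score from a time when the patient did have an SBM, so the record shows no sign that spontaneous movements had stopped.

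**Working it through.** The documents give no SBM distribution and no count of unscorable patients, so there is no stated figure to reproduce. What follows is a logical check and then a range.

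**Step 1: can an enrolled patient have no run-in SBM?** Entry needs straining and a hard stool in the run-in, so a patient with no stool at all does not qualify. A patient whose stools all followed rescue or assistance can qualify, since rescue is permitted and no unassisted stool is required. The rescue rule under Intervention allows rescue after three days without a movement, and a 7-day week with no SBM will usually contain such a gap. A zero-SBM week will therefore often contain a rescue stool that could be graded. The entry criterion excludes such a patient only if that stool is not hard, or if the criterion is read as requiring an unassisted stool.

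**Step 2: one week with no SBM.** Assumptions: counts are Poisson with mean m per week, P(0) = exp(-m); or negative binomial with k = 4 (between-patient CV 0.5), P(0) = (4/(4+m))^4. The entry requirement is ignored here, so these are upper-end figures. The count of 80 uses the Poisson column.

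| m per week | Poisson | of 80 | Neg. binomial, k = 4 |
|---|---|---|---|
| 1 | 0.368 | 29 | 0.41 |
| 1.5 | 0.223 | 18 | 0.28 |
| 2 | 0.135 | 11 | 0.20 |
| 2.5 | 0.082 | 7 | 0.14 |
| 3 | 0.050 | 4 | 0.11 |

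The means above 2 are included because entry is by complete SBMs, which are a subset of SBMs. A daily simulation in which rescue follows three dry days and displaces an SBM on that day (also an assumption) gives 47%, 32% and 22% at 1, 1.5 and 2 per week.

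**Step 3: a 4-week window with no SBM.** Poisson: exp(-4m). Negative binomial: (4/(4+4m))^4.

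| m per week | Poisson | Neg. binomial, k = 4 |
|---|---|---|
| 1 | 0.018 (1.5 of 80) | 0.063 (5 of 80) |
| 1.5 | 0.0025 | 0.026 |
| 2 | 0.0003 | 0.012 |
| 3 | <0.0001 | 0.004 |

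The rescue simulation gives 5.0%, 1.1% and 0.3% at 1, 1.5 and 2 per week. A wider spread (k = 2) gives 11%, 6% and 4%. At 0.5 SBMs per week the Poisson figure is 13.5%.

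**Step 4: what LOCF does.**
- Missing baseline: no earlier value exists, so there is no change score.
- Empty weeks 1–4: the baseline is carried forward and the recorded change is 0.
- Empty weeks 5–8: the weeks 1–4 mean is carried forward, so any earlier improvement is recorded as kept.

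**Step 5: precision, as illustration only.** Losing 22% of 40 leaves about 31 per arm. For a two-sample t-test at an effect of 0.65 SD, power falls from 0.82 to 0.71. The 0.65 SD is not in the documents, and no outcome in this trial was formally powered.

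**The case against.** The strongest case against has four parts.

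1. The text subtracts the score from the first visit and does not call it a run-in mean. If it is a single rating at screening, there is no zero denominator at baseline. This stands as an ambiguity. But both outcomes are titled as changes from baseline in a per-SBM mean, and Table 1 marks that same mean at Week 0. The other reading would subtract a one-off rating from a 4-week average, so the text needs fixing either way.

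2. The run-in entry criterion and the looser link between complete SBMs and SBMs pull the one-week figures down. This stands. The Introduction's rate is background and not an entry limit, so the range must run down to 5% and may go lower.

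3. Scoring an empty window is ordinary analysis-plan detail. This stands in part. The article does fix both the formula and the missing-data rule, however, and the rule it fixes works badly for this formula.

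4. Only post-baseline gaps can bias the comparison, and these are rare at 1 to 2 SBMs per week. This stands, except with very low rates or wide variation between patients.

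A reader might also infer that the most severe patients are removed from the analysis after baseline, leaving a sham mean based only on those who did better. The documents do not support that: under LOCF the patient stays in the Full Analysis Set with an earlier score. The failure is masked; the patient is not excluded.

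**Conclusion.** The point holds in a limited form. Both scores are undefined at zero SBMs, and LOCF is the wrong tool for either gap.

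At baseline the loss is one of precision and population, not of balance between arms. It depends on baseline being the run-in per-SBM mean and on assisted stools satisfying the entry criterion. Its size is unknown: 5% to 37% under Poisson for 3 down to 1 SBMs per week, and less if entry requires a hard, unassisted stool.

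After baseline the affected share is small at 1 or more SBMs per week: under 2% under Poisson, and about 6% at most with a between-patient CV of 0.5. It passes that only with wider spread or lower rates. Those few windows can depend on treatment and would be recorded as unchanged or still improved.

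This concerns two secondary outcomes. It does not touch the primary outcome, for which zero SBMs simply means zero complete SBMs.

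**What to change.** - **Baseline.** State that the first-visit score in items 2 and 3 is the per-SBM mean over the 1-week run-in, in line with Table 1.
- **Model.** For each outcome, analyse the run-in, weeks 1–4 and weeks 5–8 per-SBM means together in a longitudinal mixed model. Treat the run-in mean as one of the outcomes, with a common baseline mean across arms and a treatment effect at each later window. A patient with no run-in SBM then still contributes through the later windows.
- **Empty windows.** Do not apply LOCF to a window with zero SBMs. Report the number of such windows by arm, and the number of patients without a run-in SBM.
- **Sensitivity.** Add a rank-based analysis that gives zero-SBM windows the worst rank. It is needed because the mixed model treats those windows as missing at random, which is doubtful when emptiness reflects non-response. State the direction of worst for stool form.

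The cost is analysis wording only; the defecation diary already holds the data. The one drawback is that a model estimate replaces the simple mean change.

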#### MicroRNAs High-Throughput Sequencing Analysis

High-throughput sequencing using stool samples will be performed for miRNA expression profiling to determine candidate miRNA biomarkers for the efficacy of acupuncture (24–26). Fecal miRNA levels initially will be determined using a TaqMan low-density array in pooled samples. Markedly altered miRNAs in participants will subsequently be validated using quantitative real-time polymerase chain reaction on individual samples. Agilent 2100 will be used for detection, and after qualification, these fragments will be sequenced using the Illumina NOVA platform. Bowtie software will be employed to classify and annotate sRNA, and unannotated reads will be obtained by comparing clean reads with the database. The difference between SCC patients and healthy volunteers at baseline will be analyzed to explore potential biomarkers associated with the development of SCC. Within the pool of biomarker candidates related to SCC, the difference between VA and SA at week 4 will be compared, to determine biomarkers related to the clinical efficacy.

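### Straining and stool-form changes do not clearly subtract a like-for-like baseline, and the arm comparisons of clinical scores and miRNA make no baseline adjustment: precision is lost, without bias

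*Protocol article*

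**What the plan says.** Secondary Outcome Measurement, items 2 and 3, are both titled as changes from baseline in a per-SBM mean. For straining, the follow-up term is obtained by "dividing the total score of straining all SBMs by the sum of SBMs times in weeks 1–4 and 5–8", and the baseline enters through "which will then be subtracted by the score of straining in the first visit". For stool form the mean is formed in the same way and "then will be subtracted by the score of BSFS in the first visit".

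Table 1 lists both per-SBM means with a mark at Baseline (Week 0) and none at Enrollment (Week −1). Trial Design has the study "preceded by a 1-week run-in phase after the screening visit". The Inclusion Criteria already judge bowel symptoms over that run-in: "Two or fewer CSBMs per week, exertion in defecation, and lumpy or hard stools".

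For quantitative clinical data, Clinical Data Analysis says that, under normality, "we will use the analysis of variance to detect the difference between groups; otherwise, the Mann-Whitney test will be used". For miRNA, after candidates are selected by comparing patients with healthy volunteers at baseline, "the difference between VA and SA at week 4 will be compared, to determine biomarkers related to the clinical efficacy". Collection of Fecal Samples has all 80 patients give stool before and after treatment, and objective 3 is about how miRNA changes relate to symptom improvement and the microbiota.

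**The concern.** A change score is easiest to interpret when both terms are the same kind of quantity. Here one term is an average over four weeks of bowel movements, and the other is a score attached to a visit, with no statement of how that score is obtained. The titles and Table 1 point to a different baseline, the per-SBM mean at Week 0. A programmer following the formula and one following Table 1 could therefore compute different outcomes.

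Separately, the article names its between-arm tests, and none of them uses the baseline value as a covariate. For miRNA the arm comparison uses week-4 levels only, so each patient's pre-treatment level plays no part in it, even though the objective is worded in terms of change.

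What is at stake is precision in a trial of 40 per arm whose size was not derived from a power calculation. The primary responder outcome is not touched by the first-visit definition.

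**Working it through.** **The plan's own figure.** There is none to reproduce here: the sample-size section gives no effect size, SD, correlation or power. All variance and power inputs below are assumptions, shown over a range.

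**Step 1. The two baseline definitions side by side.**
- Formula (items 2 and 3): the score in the first visit.
- Titles of items 2 and 3, and Table 1: a per-SBM mean, marked at Week 0.

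If the first visit is the screening visit, it precedes the run-in, and Table 1 schedules no such score there. If it is Week 0, the wording is still a score and not a per-SBM mean. On either reading the formula does not clearly match the titles and Table 1.

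**Step 2. Cost of not adjusting.** Let the baseline and follow-up values have equal variance 1 and correlation r. The variance relevant to the arm contrast is:
- follow-up only: 1
- change score: 2(1 − r)
- ANCOVA: 1 − r²

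The reduction from ANCOVA is 1 − (1 − r²)/[2(1 − r)] = (1 − r)/2 against change scores, and r² against follow-up only.

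| r (assumed) | Change score | Follow-up only | ANCOVA | Cut vs change | Cut vs follow-up only |
|---|---|---|---|---|---|
| 0.3 | 1.40 | 1 | 0.91 | 35% | 9% |
| 0.5 | 1.00 | 1 | 0.75 | 25% | 25% |
| 0.7 | 0.60 | 1 | 0.51 | 15% | 49% |

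**Step 3. The same in power.** With 40 per arm, two-sided alpha 0.05 and an assumed true difference of 0.5 SD:

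| r (assumed) | Change score | Follow-up only | ANCOVA |
|---|---|---|---|
| 0.3 | 47% | 61% | 65% |
| 0.5 | 61% | 61% | 73% |
| 0.7 | 82% | 61% | 88% |

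**Step 4. What a single-rating baseline would add, if that is what is meant.** Assume between-patient variance 1, within-patient variance per SBM 1, true correlation 0.7 between phases, 12 SBMs in the follow-up window and k SBMs behind the baseline. The change-score variance is (1 + 1/k) + (1 + 1/12) − 2(0.7):
- k = 1: 2 + 1.083 − 1.4 = 1.68
- k = 2: 1.5 + 1.083 − 1.4 = 1.18
- k = 3: 1.333 + 1.083 − 1.4 = 1.02

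Follow-up only has variance 1 + 1/12 = 1.08. So in this scenario, subtracting one noisy rating (1.68) is worse than ignoring baseline. ANCOVA with the same one-rating baseline gives 1.083 − 0.7²/2 = 0.84, because the covariate is down-weighted according to its noise.

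**Step 5. Is the arm comparison biased?** No. In 20,000 simulated null trials of 40 per arm, with a one-SBM baseline and the Step 4 assumptions, type I error was 5.0% and the mean arm difference 0.000.

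**The case against.** The best defence is that the first-visit wording is loose drafting for the Week 0 value. Both titles and Table 1 support that, and randomized comparisons of change scores or of week-4 levels are valid. The full analysis plan is not shown and could add covariates. This defence limits the point but does not remove it: the formula as printed disagrees with Table 1, and the unadjusted tests and the week-4 miRNA comparison are stated choices, not omitted detail.

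Four stronger readings are tempting, and the document does not support them.
- *The baseline is a value recalled at screening.* The article does not define the first visit, and does not say that the score is recalled or rests on one bowel movement.
- *A single rating multiplies the noise by a large fixed factor.* The within-patient noise ratio is (1 + 1/12)/(1/k + 1/12): 2.6 with three run-in SBMs, 1.86 with two and 1.0 with one. The Introduction associates severe constipation with fewer than two weekly SBMs, so the higher figure cannot be presumed. Inclusion limits complete SBMs and not all SBMs, so k is simply unknown.
- *Chance baseline imbalance passes straight into the result.* With equal variances, an imbalance d moves a change score by (r − 1)d and a follow-up-only comparison by r·d. At r = 0.5 that is half of d in size, in opposite directions.
- *Baseline is ignored throughout.* All four secondary outcomes are defined relative to baseline; what is missing is covariate adjustment.

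Two practical objections also stand. The miRNA work starts with pooled samples, where a per-patient baseline regression is impossible. And a run-in per-SBM mean is undefined for a patient with no SBM in that week.

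**Conclusion.** The point holds as a definitional mismatch in two secondary outcomes plus an inefficient choice of analysis. The change formulas for straining and stool form should be reconciled with the titles and Table 1. If the first-visit score is a single rating, it adds avoidable noise equally in both arms.

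The unadjusted comparisons are valid but less precise than they need be. ANCOVA would cut residual variance by 35%, 25% and 15% against change scores, and by 9%, 25% and 49% against week-4 levels alone, at correlations of 0.3, 0.5 and 0.7. These sizes rest on equal variances and on correlations that the document does not give. The Step 4 figures rest further on assumed SBM counts and within-patient variance, and serve only as illustration.

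A reader might infer a biased treatment comparison. The document does not support that: the mismatch is the same in both randomized arms, and the consequence is lost precision.

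**What to change.** 1. Replace the first-visit score in items 2 and 3 by the per-SBM mean over the run-in week, identified as the Week 0 value in Table 1. State a rule for patients with no run-in SBM.
2. Analyse straining, stool form and PAC-QOL by ANCOVA: follow-up value on arm plus baseline value, with straining and stool form done for each four-week window.
3. For miRNAs measured on individual samples, regress week-4 log expression on arm plus the patient's own baseline log expression. Leave the pooled stage as a screening step.

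The cost is wording in the protocol and analysis plan, best settled before unblinding. No new visit or sample is needed: the run-in already assesses straining and stool form for eligibility, and the pre-treatment stool sample is already planned. One thing to confirm is that the run-in diary records both scores for each SBM, since the article does not say so outright.
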